## Abstract

**Background:**

An aging population and better management of various heart diseases explain the exponential growth in incidence and prevalence of chronic heart failure, with poor prognosis and heavy health costs. Medical management is codified in international guidelines. The management of heart failure in over-80 year-old patients follows these guidelines, but no clinical trials have been able to confirm benefit. Moreover, registries show down-prescription of heart failure treatments in the elderly and over-80s.

**Methods/Design:**

We present the design of the HF-80 ("Is there benefit in optimising heart failure treatment in over-80 year-old patients?") study, which is a prospective randomised open-label clinical trial with blinded end-points, designed to evaluate the effect of optimising management by adhering to guidelines in over-80 year-old heart failure patients. Patients over 80 years of age admitted with acute heart failure will be included. The primary endpoint is to assess quality of life at 6 months on the Minnesota questionnaire. The secondary endpoints are to assess the effect of optimised management on quality of life, mortality, readmission for acute heart failure, cardiac fibrosis and economic data at 12 months. 80 patients will be included, divided into 2 groups: group A, with usual heart failure management by general practitioners; and group B, with optimised management based on international guidelines.

**Discussion:**

It is necessary to assess the benefit of guidelines in over-80 year-old heart failure patients because of the fragility of this population and the elevated risk of iatrogenic complications.

**Trial Registration:**

Clinical trials.gov number: NCT01437371.

## Background

An aging population and improved management of various heart diseases involving ischemic aetiologies explain the growth in incidence and prevalence of chronic heart failure (HF) [1], with high complication rates [2,3] and heavy costs (more than 1% of total health care costs in industrialised countries). Mean age at diagnosis of HF was 70 years in the Framingham cohort [3]. Incidence and prevalence increase exponentially with age [3].

Angiotensin-converting enzyme inhibitors (ACEi) [4,5] beta-blockers [6,7], mineralocorticoid receptor antagonists [8], and angiotensin receptor blockers [9,10] provide first-line therapeutic management of HF as recommended in international guidelines [11,12]. These, however, are based on studies conducted on younger patients (mean age between 61 and 71 years: Table 1). Clinical management of over-80 year-old HF patients conforms to these guidelines, but no clinical trials have been able to confirm their benefit in this population. Comorbidity and iatrogenic complications may impair the effect of common treatments. Recent clinical trials in HF management continued to recruit younger subjects, because of the need to highlight a beneficial effect of the treatment tested [13-15]. Some studies have reported benefit with such treatments in this kind of population [16,17]. Registries and observational studies highlighted down-prescription, especially for ACEi and beta-blockers, in elderly and over-80 year-old patients [18,19].

**Table 1 T1:** Mean age of main studies in HF management

Clinical studies	Ages of placebo Group (years old)	Ages of studied drug group (years old)
*HF subgroup of Hyvet (hypertension study)*	83.5 ± 3.1	83.6 ± 3.2

*Seniors*	76.1 ± 4.8	76.1 ± 4.8

*Charm-Alternative*	66.8 ± 10.5	66.3 ± 11

*Merit HF*	63.7	63.9

*Charm-Added*	64.1 ± 11.3	64.0 ± 10.7

*Consensus*		71

*Solvd*	59.1	59.1

*Cibis II*	61	61

*Emphasis-HF*	68.6 ± 7.6	68.7 ± 7.7

*Ephesus*	66 ± 12	64 ± 11

*Rales*	65 ± 12	65 ± 12

*Atlas study*	Low-dose of lisinopril: 63.6 ± 10.3	High-dose of lisinopril: 63.6 ± 10.5

*Elite-1 trial*	Losartan: 74(5-8)	Captopril: 73 (6-1)

*Elite-II trial*	Losartan: 71.4 (6-7)	Captopril: 71 (6-9)

*Shift*	60.1 ± 11.5	60.7 ± 11.2

*Copernicus*	63.4 ± 11.5	63.2 ± 11.4

*Valiant*	Captopril: 64.9 ± 11.8 Valsartan: 65 ± 11.8	Valsartan + Captopril: 64.6 ± 11.9

*Dig*	63.9 ± 11.7	63.8 ± 11

## Methods/Design

Heart failure management is now clearly codified for the general population, thanks to several studies and guidelines. Management of over-80 year-old HF patients, however, is simply extrapolated from their findings. No study has specifically assessed optimised HF treatment in the over-80s, where potential benefit could be counterbalanced by co-morbidity and iatrogenic complications. The HF-80 clinical trial was designed as a pilot study to investigate whether optimised management has an effect on quality of life (QOL) in over-80 year-old HF patients.

### The HF-80 Study

#### Objectives and endpoints

The primary objective of this pilot study is to assess optimised HF management, according to the guidelines of the European Society of Cardiology (ESC) [11,12], in terms of impact on QOL in over-80 year-old patients at 6 months.

The secondary objectives are to evaluate the effect of optimised management on:

• Quality of life at 12 months

• Mortality at 12 months

• Readmission for acute HF at 12 months

• Cardiovascular events at 12 months

• Cardiac fibrosis, evaluated by collagen peptides.

The primary assessment criterion is QOL at 6 months, assessed on the Minnesota Living with Heart Failure Questionnaire (LHFQ) [20].

The secondary assessment criteria are QOL at 12 months, measured by both the SF 12 [21] and LHFQ [20] (to check which scale is most suited to this population), mortality at 12 months, number of readmissions for acute HF, cardiovascular events at 12 months, evolution in New York Hospital Association (NYHA) class (at baseline, 6 months and 12 months), and evolution in 6-minutes walking test (6MWT) (at baseline, 6 months and 12 months). Finally, an analysis of the medical and economic interest of this support will be conducted.

This pilot study will also help lay the groundwork for a French national multicentre study of the management of octogenarian HF patients to find what support is most appropriate.

#### Study design

The HF-80 pilot study is a prospective randomised single-centre open-label clinical trial with blinded endpoints. Current lack of knowledge regarding management for this population requires a pilot study, to harvest data before starting a clinical trial to assess mortality. The study population is over-80 year-old patients recently admitted for acute HF. Inclusion and exclusion criteria are listed in Table 2.

**Table 2 T2:** Inclusion and exclusion criteria in HF 80 study

Inclusion criteria:	
	Aged over-80 year-old subjects
	Hospitalized for an acute heart failure
	Left Ventricle Ejection Fraction ≤ 35%
	Evaluated life expectancy (Seattle Heart failure score) > 1 year
Exclusion criteria:	
	Dementia (evaluated by MMSE)
	Do not understand French language
	Followed with an optimized management
	With reduced mobility
	Recruited in another clinical trial or in a HF management network
	Acute HF with curable aetiology: cardiovascular surgery for coronary artery bypass graft or valvular replacement, angioplasty
	MDRD < 30 ml/min/1.73 m^2^

Dementia will be assessed by the Mini mental state examination (MMSE): patients with scores under 24/30 will not be included. For the very elderly, a preliminary walking test will be performed, to exclude patients with reduced mobility, who are moreover very often subject to dementia.

#### Randomisation

Included patients will be randomly allocated to either arm in a 1:1 ratio. The randomisation list is generated by minimisation [22] to maintain better balance than with traditional block randomisation. Stratification will be performed on gender (female/male), readmission (yes/no) and residence (at home/not at home). When a patient is considered eligible and informed consent has been obtained, randomisation will be performed automatically (on software) by an independent statistician.

#### Investigation Procedure

Over-80 year-old patients will be recruited and randomised into 2 groups of 40 (Figure 1):

**Figure 1 F1:**
[figure not shown]
**Flow chart describing HF 80 study design**. HF: heart failure.

• Group A: "usual care" management by the patient's usual general practitioner (GP) and cardiologist;

• Group B: "optimised" management strictly adhering to ESC guidelines [11,12], performed by the patient's usual GP and cardiologist plus day-hospital.

Patients will be included in HF-80 at discharge from acute HF care. Before inclusion, trans-thoracic echocardiography will confirm that left ventricle ejection fraction is under 35% and that no exclusion criteria are present. During hospital care, patients of both groups will receive the same treatments, so far as possible using all HF therapeutics; different hospital treatment according to group would not be ethically acceptable. Mean hospital stay is about 10 days, which is too short to induce bias, as medical management optimisation applies only after discharge. Optimised management will be assessed with long-term prognosis.

An identical assessment is to be performed at baseline and at 12 months for all patients (groups A and B) (Figure 2):

**Figure 2 F2:**
[figure not shown]
**Flow chart describing HF 80 study investigational procedure**. CE: clinical examination; EKG: electrocardiogram; MMSE: mini mental state examination; QOL: quality of life scale; 6MWT: 6 minutes walking test; Seattle HF: Seattle heart failure score; TTE: transthoracic echocardiography.

• Clinical examination: NYHA class; weight; height; heart rate; blood pressure; right, left or both HF symptoms; triggering factor; cardiovascular risk factors; thyroid pathologies; personal cardiovascular history;

• Quality of life questionnaires (LHFQ [20], SF 12 [21]);

• Six-minutes walking test (6MWT);

• Electrocardiogram (EKG);

• Transthoracic echocardiography (TTE);

• Blood test (haemoglobin, kaliaemia, natraemia, liver assessment, bilirubin, Modification in Diet Renal Disease (MDRD) [23], N-Terminal of pro-Brain Natriuretic Peptide (NT-pro-BNP), and nutritional tests (C-reactive protein, albumin, prealbumin and orosomucoid);

• Renin, aldosterone and collagen peptides [type 1 collagen telopeptide (ICTP), aminoterminal propeptide of type I procollagen (PINP), aminoterminal propeptide of type III procollagen (PIIINP)], and galectin 3;

• Mini mental state examination (MMSE) [24].

During primary hospital care for acute HF and at discharge, both groups will have the same management with initiation of the same treatments, following guidelines [11,12].

Group A subjects will be followed up by their usual GP and cardiologist without any day-hospital care ("usual care" management). The GP and cardiologist will manage treatment optimisation as they are used to doing.

Group B subjects will have the same management as group A but will also receive day-hospital care. The first 3 visits will be at 3 weekly intervals, except in case of unstable HF, and then every 6 weeks for 12 months, to optimise treatment.

During each day-hospital visit in group B, certain data will be recorded to optimise HF management:

• Clinical examination (NYHA class, HF symptoms, blood pressure, heart rate);

• Blood sample (kaliaemia, MDRD [23], NT-pro-BNP);

• Electrocardiogram;

• Optimised treatment doses, if possible, for ACEi, beta-blockers, angiotensin receptor blocker and mineralocorticoid receptor antagonist.

All the visits and contents are described in Table 3.

**Table 3 T3:** Schedule of visits and contents

	Group A		Group B					
	***Enrollement hospitalization***	***Month 12 visit***	***Enrollement hospitalization***	***Day hospital visits***	***Month 3 visit***	***Month 6 visit***	***Month 9 visit***	***Month 12 visit***

QOL questionnaires (LVHQ, SF12)	X	X	X			X		X

Clinical examination (BP, HR, weight, NYHA)	X	X	X	X	X		X	X

EKG	X	X	X	X	X	X	X	X

6MWT	X	X	X					X

Na, Hb, SGOT, SGPT, Bili	X	X	X					X
K, MDRD, NT-pro-BNP	X	X	X	X	X	X	X	X
PCR, oroso, alb, prealb	X	X	X					X

TTE	X	X	X		X	X	X	X

Blood laboratory	X	X	X		X	X	X	X

Treatments	X	X	X	X	X	X	X	X

BP: blood pressure; HR: heart rate; EKG: electrocardiogram; MMSE: mini mental state examination; QOL: quality of life; 6MWT: 6 minutes walking test; Seattle HF: Seattle heart failure score; TTE: transthoracic echocardiography; CRP: C reactive protein; oroso: orosomucoid; alb: albumin; prealb: prealbumin; MDRD: Modification in Diet Renal Disease; NT-ProBNP: N terminal pro brain natriuretic peptid; K: kaliemia; Na: sodium blood concentration; Hb: hemoglobin; bili: biliubin; SGPT: Serum Glutamopyruvate Transferase, SGOT: Serum Glutamooxaloacetate Transferase.

Patients in both groups will have a notebook, for 12 months. GPs and cardiologists will note all changes in treatment and management.

#### Transthoracic echocardiography analysis

TTE will be performed using a 2.5 MHz probe (VIVID 9, General Electrics), by a single operator [25], at inclusion and at 12 months, in both groups. TTE will also be performed at 3, 6 and 9 months for group B in day hospital, and according to "usual management" criteria for group A.

The following measurements will be taken in each subject:

2D/MM modes: Right ventricle (RV) diameter (mm); interventricular septum thickness at end diastole and end systole (mm); left ventricle (LV) posterior wall thickness at end diastole and end systole (mm); LV diameter at end diastole and end systole (mm); LV volumes at end diastole and end systole (ml); LV ejection fraction measured by the biplane Simpson method (%); LV mass index (g/m2); inferior vena cava diameter (mm); left and right atrium areas (cm^2^); RV volume; RV ejection fraction; TEI myocardial performance index; and tricuspid annular plane systolic excursion (TAPSE).

Doppler modes: transmitral flow, including peak E wave (cm/s), peak A wave (cm/s), E/A ratio, E-wave deceleration time (m/s); pulmonary venous waveforms, including peak systolic (S) velocity, peak anterograde diastolic (D) velocity, and S/D ratio; VP, Color M-Mode flow propagation velocity; relaxation isovolumic time (m/s); cardiac output, tricuspid E wave; tricuspid regurgitation (none/mean/moderate/severe); systolic pulmonary arterial pressure; mitral regurgitation (none/mean/moderate/severe); and dp/dt for left and right ventricle.

Doppler tissue imaging mode: lateral and septal E' wave and A wave at mitral annulus (cm/s), lateral and septal S wave at mitral annulus (cm/s); S' and E' wave at tricuspid annulus (cm/s).

2D-Strain mode: Loops obtained by 2D on 3 cycles, with apical 4-cavities, 3-cavities, 2-cavities and parasternal short axis views, with frame rate > 60 frames/s.

#### 6-minutes walking test

This will be performed for each patient at inclusion and at 12 months, and also at 6 months for group B [26]. The test will be made in hospital on a 60-metre track. The patients will be requested to walk at their tolerance threshold for 6 minutes. Before the beginning of each test, respiratory frequency, heart rate, blood pressure and effort perception on the Borg scale [27,28] will be measured. At the end of each test, the same parameters will be measured again. The final result of the 6MWT is the total distance covered (metres) in 6 minutes.

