#### QOL scales

It was decided to implement two QOL questionnaires (LHFQ [20] and SF 12[21]) to assess which is more adapted to over-80 year-old HF patients. Both are well-validated and widely used. The SF12 is used on a daily basis in the geriatric department of our hospital and maybe more adapted to the elderly. A second endpoint is to assess the efficiency of this shorter QOL questionnaire, SF12, as compared to the LHFQ, in a very elderly population. They will be completed at inclusion and at 12 month for each subject. QOL scales will be sent to all participants (group A and B) at 6 months (before the 6 month visit for group B) and will be filled in by the patients without any help from medics or paramedics (to avoid bias).

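### The 6-minute walk is a secondary criterion at 6 months but is scheduled then in group B only, so the arms cannot be compared at that time; for NYHA class at 6 months, no group A data source is documented

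*Protocol article*

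**What the plan says.** Under Objectives and endpoints, the secondary criteria include "evolution in 6-minutes walking test (6MWT) (at baseline, 6 months and 12 months" and "evolution in New York Hospital Association (NYHA) class (at baseline, 6 months and 12 months". Neither is limited to one arm. Statistical Considerations says in general terms that primary and secondary endpoints are compared between the randomised groups.

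The section on the walking test gives the collection schedule: "This will be performed for each patient at inclusion and at 12 months, and also at 6 months for group B". It adds that the test is done in hospital on a 60-metre track.

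The other statements on who is seen when are these:

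- Investigation Procedure, common assessment: "An identical assessment is to be performed at baseline and at 12 months for all patients (groups A and B".
- Investigation Procedure, control arm: "Group A subjects will be followed up by their usual GP and cardiologist without any day-hospital care".
- Investigation Procedure, day-hospital visits in group B: "The first 3 visits will be at 3 weekly intervals, except in case of unstable HF, and then every 6 weeks for 12 months". NYHA class is recorded at these visits.
- Text after Table 3, on the patient notebook kept in both arms: "GPs and cardiologists will note all changes in treatment and management".
- QOL scales: "QOL scales will be sent to all participants (group A and B) at 6 months (before the 6 month visit for group B".

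Table 3 gives group A two columns, enrolment and month 12. Its 6MWT row has no month 6 mark even for group B. Its clinical examination row, which contains NYHA, has an empty month 6 cell for group B.

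**The concern.** A criterion listed at 6 months for the trial, under a plan to compare secondary endpoints between groups, needs a 6-month value in both arms. For the walk, the article schedules that value in one arm only. The criterion and the schedule cannot both be carried out as written.

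The remaining 6-month walk result would be a change from baseline within group B. Patients enter at discharge from acute heart failure care, when walking capacity may be depressed by the episode itself. Some improvement over the next six months could occur under any management. Without a control value, that part cannot be separated from the effect of optimised care. The pilot is also meant to prepare a national multicentre study, so an uncontrolled improvement could feed into its planning.

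**Working it through.** **Inputs.** Two groups of 40 (Investigation Procedure). Loss allowance 15%, LHFQ difference 20, SD 25, two-sided alpha 0.05, power 90% (Statistical Considerations).

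**The plan's own figure.** The only stated sample size is for the 6-month LHFQ.

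- Normal approximation: n per arm = 2 × (1.960 + 1.282)² × (25/20)² = 32.8, so 33. Then 33/0.85 = 38.8, so 39 per arm and 78 in total.
- t-test: 33.83, so 34 per arm. Then 34/0.85 = 40 per arm and 80 in total, which matches the article.

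This figure is sound and does not bear on the walking test. It gives the evaluable number used below: 40 × 0.85 = 34 per arm.

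**Count of scheduled values.**

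| Criterion and time | Group A | Group B |
|---|---|---|
| 6MWT, 6 months (walking-test section) | 0 of 40 | up to 40 (34 after loss) |
| 6MWT, 6 months (Table 3) | none shown | none shown |
| NYHA, 6 months | no collection described | up to 40, from a day-hospital visit near month 6 |
| 6MWT and NYHA, 12 months | 40 (34 after loss) | 40 (34 after loss) |
| LHFQ, 6 months | mailed to all 40 | mailed to all 40 |

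**NYHA in group B near month 6.** The visit schedule can be read in two ways, counting weeks from discharge:

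- Visits every three weeks: weeks 3, 6, 9, then 15, 21, 27, 33.
- Three weekly visits: weeks 1, 2, 3, then 9, 15, 21, 27, 33.

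Month 6 falls at 365.25/7/2 = 26.1 weeks. Both readings give a visit at week 27, 0.9 weeks later. The empty month 6 cell in Table 3 therefore does not leave group B without NYHA, and any gap is in group A.

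**Other possible sources in group A at 6 months.**

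- The mailing carries quality-of-life scales. It cannot carry a walk on a hospital track, and NYHA class belongs to the clinical examination.
- The notebook is described as a record of changes in treatment and management, not of NYHA class or walk distance.
- Day-hospital visits are ruled out for this arm.
- The usual GP or cardiologist could record NYHA class, but the article does not ask for it.

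**What a group B change would estimate.** Mean change in B = recovery after the episode + effect of optimised care. With no group A value at that time, the first term cannot be subtracted.

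**The case against.** The strongest reply separates the two criteria. For the walk, the article itself states the arm limit. For NYHA no sentence does. The common assessment at baseline and 12 months is not said to be the only one, and the absence of day-hospital visits does not stop the usual doctors from recording NYHA class. The one schedule without a group A contact at month 6 is Table 3, and it is incomplete: it also omits the 6-month mailing to group A that the QOL section confirms. This reply stands. A reader might infer that both 6-month comparisons are lost, with 0 of 40 NYHA values in group A. The documents support that count for the walk only. For NYHA they show only that no source is described.

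A second reply is that the 6-month between-arm test is inferred. The abstract places the secondary endpoints at 12 months, the criteria speak of evolution, and the statistics section has one general sentence on group comparisons and names no 6-month walk test. This is partly right, and the point should be read as a conflict between a listed time point and its schedule. It does not remove the conflict, because the criterion carries no arm limit and the general sentence covers secondary endpoints.

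A third reply is that random effects models accept unequal visits. They do, but here the group A cell is empty by design. The model would supply a group A value at 6 months only by assuming a straight line from baseline to month 12.

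Finally, nothing in the article proposes to present the group B change as a treatment effect, and a descriptive within-arm value is legitimate in a pilot. That is fair: the risk lies in how the result might later be read.

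**Conclusion.** The point holds for the walking test. The 6-month between-arm comparison cannot be made, with 0 of 40 scheduled values in group A against up to 40 in group B. For NYHA class at 6 months the conclusion is weaker: the comparison has no documented data source in group A, though no text excludes one.

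The conclusion rests on the prose of the endpoint and walking-test sections. Table 3 agrees on group A but is too incomplete to carry the point, and for the group B walk it disagrees with the prose. It is assumed that the general sentence on comparing secondary endpoints covers the walking test and NYHA at each listed time.

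The effect is confined to one intermediate time point of secondary criteria in a pilot study. It would be wrong to extend it to the primary endpoint, since the 6-month LHFQ is mailed to both arms and its sample size of 80 is reproduced. The 12-month comparisons of 6MWT and NYHA, planned in both arms, also stand. The plan should be corrected because the change is nearly free.

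**What to change.** - **Objectives and endpoints:** limit the between-arm 6MWT criterion to baseline and 12 months. Do the same for NYHA class, unless a 6-month collection in group A exists, in which case state it.
- **6-minutes walking test:** drop the 6-month walk in group B, or keep it and label it a descriptive within-arm value that is not a treatment effect.
- **Statistical Considerations:** compare 12-month 6MWT between arms with baseline 6MWT, already collected, as covariate.

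The cost is wording in three sections, with no added patients, visits or assessors and no change to N = 80. Dropping the group B walk saves up to 40 tests and loses one descriptive time point in that arm. Keeping it as descriptive loses nothing.
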